### Primary outcome

The primary outcome measure is change in ambulatory activity (steps per day) at 48 months, assessed by accelerometer (Actigraph GT3X+) with an intermediary assessment at 12 months. Participants are asked to wear the accelerometer on a waistband (in the right anterior axillary line) for seven consecutive days during waking hours following their baseline and follow-up visits. In addition, participants are asked to fill in a log sheet each day that they wear the accelerometer indicating time the accelerometer was taken off at night, time they went to sleep, time they woke up and time the accelerometer was attached. At the end the seven days of wear, participants are asked to return the accelerometer and the log sheet to the research team in a pre-paid envelope. Raw acceleration data are captured and stored at 100 Hz. Data processing will be undertaken on commercially available analysis tools. At least three days valid wear is required to count as a valid recording. Non-wear time is determined by one hour or more of consecutive zero counts. Due to the potential for bias between groups in factors used to acquire valid accelerometer data, average wear time and the number of valid days will be included as covariates in the analysis.

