### Sample size

#### Primary outcome

For 1-beta = 0.8, alpha = 0.025 (allowing for 2 a priori comparisons against control conditions), SD = 4000 steps/day and a drop-out of 30 %, we require 436 per group (1308 in total) to detect a 1000 steps/day difference in change in ambulatory activity (equivalent to 10 mins walking/day or 70 mins walking/week) between the intervention groups and control group. Assuming 25 % of participants in the total cohort are SA we have an 80 % power to detect around a 2000 steps/day difference when comparing two intervention comparisons to the control group (alpha = 0.025) in the SA population.

Several intervention studies with a follow-up of between 3 to 12-months reported a standard deviation of change in ambulatory activity of around 3000 to 4000 steps per day in individuals with T2DM, prediabetes or in sedentary individuals [32, 57–59].Therefore we have anticipated a standard deviation of change of 4000 steps per day. An intervention effect of 1000 steps was considered the minimum clinically significant difference between groups and equates to around a 4 % difference in the risk of cardiovascular morbidity and mortality [13].

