### Data analysis

Analysis will involve two *a priori* comparisons; both intervention groups will be compared to the control group. Should any of these comparisons reveal a significant difference, then a third *a priori* comparison will be undertaken by comparing the difference between intervention groups - this will be included as a secondary analysis. Multiple linear regression analysis will be used to investigate the differences in the change in physical activity level achieved between groups at 48 months, after adjusting for potential areas of bias between groups, valid accelerometer wear time and the number of valid wear days. Analysis will be conducted on the cohort as a whole and stratified by ethnic group; interaction terms will be used to quantify the effect of ethnic group. We will also use interaction terms to assess whether the effects of the interventions are modified of gender, age, ethnicity, family history of T2DM or whether prediabetes status was confirmed at baseline; significant interactions will followed by stratified analysis. We will also assess change in physical activity at 12 months as a secondary outcome. The primary analysis will be based on analysing those with complete data at each time point in the group to which they were randomised. A sensitivity analysis will be undertaken to assess the impact of imputing missing data through multiple imputation and through a per-protocol analysis by removing those that failed to attend the initial Walking Away session in both intervention groups; per-protocol analysis for the Walking Away Plus group will be defined as removing those that that failed to attend the initial Walking Away session OR those that failed to register for or actively stopped their text messaging support via the STOP function within the first 2 months.

Analysis of secondary biochemical and anthropometric outcomes will be analysed using the same strategy and at the same time-points as that described for the primary outcome. Differentials in the time to T2DM between groups will be plotted using the Kaplan–Meier method for comparing survival curves; the log rank test will be used to assess for differences between the groups.

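### The complete-case primary analysis at 48 months, with 30% drop-out expected, makes no use of the 12-month step count and so needs a stronger missing-data assumption than the collected data require

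*Protocol article*

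**What the plan says.** All references are to the protocol article.

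- **Model (Data analysis):** "Multiple linear regression analysis will be used to investigate the differences in the change in physical activity level achieved between groups at 48 months". The adjustments it names are accelerometer wear time, the count of valid days and otherwise unspecified sources of bias. The 12-month step count is not among the named covariates.
- **Population (Data analysis):** "The primary analysis will be based on analysing those with complete data at each time point in the group to which they were randomised".
- **Other missing-data handling (Data analysis):** "A sensitivity analysis will be undertaken to assess the impact of imputing missing data through multiple imputation". The variables in the imputation model are not given, which is normal for an article.
- **12-month steps:** the Primary outcome section provides the 48-month accelerometer measure "with an intermediary assessment at 12 months", and Table 4 lists it at 0, 12 and 48 months. Its stated analytic use is separate: "We will also assess change in physical activity at 12 months as a secondary outcome".
- **Expected loss (Sample size, Primary outcome):** "SD = 4000 steps/day and a drop-out of 30" per cent, with 436 per group and 1308 in total, to detect 1000 steps/day.

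**The concern.** A complete-case regression of 48-month change is unbiased only if, given the covariates in the model, being missing at 48 months is unrelated to the outcome. Here there is reason to doubt that. Participants know their allocation. The two active arms receive step goals, pedometers and annual sessions, and the Plus arm also receives feedback on goal achievement. Falling short of a goal is therefore a visible experience in the active arms and much less so in the control arm, which receives a leaflet. If people who are doing poorly leave the active arms more readily than comparable controls do, the remaining active participants look better than the arm as randomised. Equal drop-out rates do not protect against this.

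The 12-month step count is likely to predict a missing 48-month value well, and it is available for everyone lost after that visit. The primary analysis sets it aside. At stake is the primary estimate and the two tests against control, judged against a difference of 1000 steps/day that the article calls the minimum clinically significant one.

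**Working it through.** **1. Reproduce the plan's sample size.** Inputs from the Sample size section: difference 1000, SD of change 4000, power 0.80, alpha 0.025 (taken as two-sided), drop-out 30%.

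n = 2 × (z₀.₉₈₇₅ + z₀.₈₀)² × (SD/difference)² = 2 × (2.241 + 0.842)² × 16 = 304.2, so 305 evaluable per arm.

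305 / 0.70 = 435.7, so 436 per group, and 3 × 436 = 1308. Both match the article. One-sided 0.025 gives 252 evaluable and 360 per group, which does not match.

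**2. How many are left out.** 0.30 × 436 = about 131 per group. 0.30 × 1308 = about 392 in total.

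**3. Simple size of the bias.** Arm mean among stayers minus arm mean among all = drop-out proportion × (stayer mean − leaver mean). Assume, since the documents give no figure, that active-arm leavers change by 500 to 1000 steps less than stayers and that controls have no such gap:

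- 0.30 × 500 = 150 steps
- 0.30 × 1000 = 300 steps

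The planned standard error is 4000 × √(2/305) = 324, so this is 0.46 to 0.93 standard errors. With no true effect, the two-sided error rate per comparison would rise from 2.5% to about 4.1% and 9.5% respectively.

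**4. Simulation over drop-out mechanisms.** Assumptions, none from the documents except the SD, the 30% and the target of 1000:

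- SD of change 4000; correlation with baseline 0.5 or 0.7; 12-to-48-month correlation 0.70 or 0.82
- True effect 1500 at 12 months and 1000 at 48 months
- 30% missing in each arm, of which none or 15 percentage points are lost at random before 12 months
- Logistic slope of −1 per 4000 steps of change (per SD for baseline)
- Baseline steps in the model; 400,000 per arm; simulation error about 10–15 steps

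The second method is a likelihood-type estimator using baseline, 12- and 48-month steps, standing in for a repeated-measures model.

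| Drop-out depends on | Complete-case | Using 12-month steps |
|---|---|---|
| Nothing, or baseline (active arm only) | 992–1012 | 988–1013 |
| 12-month change, same way in both arms | 975–1012 | 981–1011 |
| 12-month change, active arm only | 1284–1569 | 999–1009 |
| Unseen 48-month change, active arm only | 1464–1873 | 1312–1545 |

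**5. Sensitivity to the mechanism.** A second set of assumed correlations (0.65 baseline to 12 months, 0.65 for 12 to 48 months, 0.50 baseline to 48 months), with the same slope, gives:

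| Drop-out depends on 12-month change | Complete-case | Using 12-month steps |
|---|---|---|
| Active arm only, nobody lost before 12 months | 1350 | 1010 |
| Control slope half the active slope | 1164 | 1002 |
| Same in both arms | 997 | 996 |
| Active arm only, half the loss before 12 months and driven by the unseen 12-month value | 1374 | 1187 |

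In the last row, 187 of the 374 steps of bias remain, about half.

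**6. Precision.** With 436 per arm and the correlations of step 5, a smaller simulation gave a standard deviation of the estimate of 296 for complete-case and 284 when 12-month data were used, about 4% less. The case for the change is bias, not power.

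**The case against.** **The plan does not ignore missing data.** Multiple imputation is prespecified and could include the 12-month value under the same missing-at-random assumption. What is in dispute is which analysis is primary. This is fair, but a sensitivity analysis does not set the primary estimate or the tests at 0.025. If the two disagreed, the plan would give precedence to the one with the stronger assumption.

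**Bias is not certain.** The article gives 30% as a planning figure, with no split by arm or by time of loss. Random loss, loss explained by modelled baseline steps, or loss that works alike in both arms leaves the complete-case contrast essentially unbiased. This stands: neither the size nor the direction of any bias can be read from the documents.

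**A reader might infer that a repeated-measures model would remove the attrition bias.** It would do so only if data are missing at random given baseline and 12-month steps. In the simulation it left 310 to 545 steps of bias when drop-out depended on unseen 48-month change. It can do little for people lost before 12 months. The two visits are 36 months apart, so later, unseen changes in activity could well drive loss.

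**A reader might also infer that the plan discards participants who have 48-month data but no valid 12-month recording.** The words about complete data at each time point allow that reading. But the sentence directly follows the one introducing the 12-month analysis, and more naturally means that each time point is analysed in those with data for it. This is an ambiguity to clear up, not evidence of exclusion.

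**Conclusion.** The point holds in a limited form. The article fixes complete-case regression as primary, expects about 131 losses per group, and leaves an already collected predictor of the missing outcome out of the primary estimate. It therefore needs a stronger missing-data assumption than necessary.

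If drop-out depends on 12-month activity differently by arm, complete-case gave about 1160 to 1570 for a true 1000 under the stated assumptions, and using the 12-month value brought this back to about 1000 when anyone lost before 12 months was lost at random. If drop-out is random, tied to baseline or alike across arms, there is nothing material to correct. The result for baseline-dependent drop-out requires baseline steps in the model, which the article does not name as a covariate.

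Using the 12-month data was not materially worse in any scenario examined. That makes this a worthwhile, inexpensive improvement. It does not show that the planned result will be biased.

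**What to change.** 1. Make one of these the primary analysis:
   - a repeated-measures model with 12- and 48-month steps as outcomes, baseline steps as covariate, arm-by-visit terms, unstructured covariance, visit-specific wear time and number of valid days (both already required by the plan), and the 48-month contrast as the primary estimate; or
   - multiple imputation whose model includes 12-month steps.
2. Keep complete-case regression as a sensitivity analysis.
3. Add a delta-adjusted analysis for data missing not at random, because neither option in step 1 covers drop-out driven by unseen activity.
4. State that the complete-data wording does not exclude participants who have 48-month data but lack a 12-month recording.

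The cost is analysis-plan wording and slightly more programming, including a rule for wear covariates that differ by visit. The primary result would rest on missing-at-random, which is still an assumption but a weaker one than the plan now needs. Participants with no follow-up recording would still contribute no outcome to the repeated-measures model. No new data, visits or participants are needed, and 436 per group stays as it is because it already carries the 30% loss.

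### The per-protocol sensitivity analysis removes non-adherers from the active arms only, so it is open to selection bias; an attendance-based complier-average estimate should be added as the main adherence analysis

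*Protocol article*

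**What the plan says.** In the protocol article, Data analysis, the primary analysis compares complete cases as randomised, each intervention group against control. A sensitivity analysis then has two strands. One is multiple imputation. The other proceeds "through a per-protocol analysis by removing those that failed to attend the initial Walking Away session in both intervention groups".

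For Walking Away Plus the rule goes further and also removes "those that failed to register for or actively stopped their text messaging support via the STOP function within the first 2 months".

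No exclusion is given for the control group. Under Study interventions, that group receives an advice leaflet and standard care, so it has no session to miss and no text service to decline. The section on uptake and adherence lists session attendance, text registration, STOP messages and text engagement as process measures, so the data on receipt will exist.

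**The concern.** Whether a person attends is decided after randomisation and is seen only in the active arms. Some controls would also have stayed away had they been invited, but they cannot be identified and they stay in. The per-protocol contrast therefore sets a selected subset against an unselected group. If attenders would have changed their activity differently from non-attenders without any programme, that difference is counted as an intervention effect.

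Two features add to this. The filter is stricter in Walking Away Plus, so a per-protocol comparison of the two active arms would be unbalanced as well. And the analysis stands beside multiple imputation as a sensitivity analysis, although it does not test an assumption of the primary analysis. It asks a different question, without the protection of randomisation. At stake is how this secondary result is read, not the primary conclusion.

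**Working it through.** **1. The plan's own figure.** The article gives no number for adherence or for the per-protocol analysis, so the reference point is the sample size (Sample size, Primary outcome). Inputs:
- power and alpha: "For 1-beta = 0.8, alpha = 0.025", the alpha allowing for two comparisons with control;
- "SD = 4000 steps/day and a drop-out of 30" %;
- target: "to detect a 1000 steps/day difference in change in ambulatory activity";
- result: "we require 436 per group (1308 in total").

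With two-sided alpha, n = 2 × (2.241 + 0.842)² × 4000² / 1000² ≈ 304.2, so 305 per group. Then 305 / 0.7 = 435.7, so 436, which matches. Sidedness is not stated, but one-sided 0.025 gives 252, or 360 after inflation, which does not match. The per-protocol rule plays no part in this figure.

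**2. Form of the bias.** Let π be the share of adherers among those analysed, and D the difference in untreated mean change between would-be adherers and non-adherers. Take the untreated mean of non-adherers as 0, the effect in adherers as τ, and no effect in non-adherers.
- Control mean: πD.
- Mean of the active participants kept: D + τ.
- Per-protocol difference: τ + (1 − π)D.

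The bias is (1 − π)D: zero if D = 0, and negative if D is negative.

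**3. Size over an assumed range.** Neither π nor D is in the article. Bias in steps/day:

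| Share removed | D = 0 | D = 250 | D = 500 | D = 1000 |
|---|---|---|---|---|
| 10% | 0 | 25 | 50 | 100 |
| 20% | 0 | 50 | 100 | 200 |
| 30% | 0 | 75 | 150 | 300 |
| 40% | 0 | 100 | 200 | 400 |

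**4. Effect on a test with no true effect.** Take 305 controls and 305π active participants, SD 4000 and nominal two-sided 0.025. For 20% removed and D = 500:
- SE = 4000 × √(1/305 + 1/244) ≈ 344;
- the bias of 100 is 0.29 SE;
- type I error = 0.031.

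It is 0.051 for 20% and D = 1000, 0.121 for 40% and D = 1000, and 0.025 whenever D = 0.

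**5. Unequal filters.** As an illustration with no effect in either arm, suppose 20% are removed from Walking Away and 40% from Walking Away Plus, with a gap of 500 in each. The biases against control are 100 and 200. A per-protocol comparison of the two active arms would then show 200 − 100 = 100 steps/day for Walking Away Plus from selection alone.

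**6. The alternative estimator.** CACE = as-randomised difference / π, with SE ≈ 4000 × √(2/305) / π = 324 / π. For an as-randomised difference of 1000 steps/day:

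| π | CACE | SE |
|---|---|---|
| 0.9 | 1111 | 360 |
| 0.8 | 1250 | 405 |
| 0.7 | 1429 | 463 |
| 0.6 | 1667 | 540 |

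Estimate and SE scale together (1000/324 and 1250/405 are both about 3.1), so the CACE creates no evidence that the as-randomised contrast lacks.

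**7. Simulation** (20,000 replicates, 305 per arm, π = 0.8, D = 500). Mean estimates in steps/day:

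| True effect in adherers | As randomised | CACE | Per-protocol |
|---|---|---|---|
| 0 | +2 | +2 | +103 |
| 1000 | 801 | 1001 | 1102 |

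The standard error was about 405 for the CACE and 344 for the per-protocol estimate.

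**The case against.** The strongest reply is that little hangs on this analysis. It is one strand of a sensitivity analysis beside an as-randomised primary comparison, and no sample size or decision rule depends on it. That stands, and it limits the weight of the point.

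Three stronger readings are tempting, and the article does not support them.

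- *A reader might infer that the rule is shown to favour the intervention.* The direction rests on the sign of D, which is not given. The outcome is change in steps. If attenders start more active they may have less room to increase, and the programme itself asks those already above 9000 steps/day at least to hold their level. A positive gap is likely, but a zero or negative one cannot be excluded. The share removed may also be smaller among those analysed than among those randomised, if non-attenders make up much of the planned 30% drop-out.
- *A reader might infer that the two-month STOP window is too short for a 48-month outcome.* That pulls against the main argument, because a longer window would select on still more behaviour after randomisation. Table 3 also makes months 0–2 the most intensive texting phase.
- *A reader might infer that a CACE must replace the per-protocol analysis.* Its exclusion restriction requires that assignment has no effect on initial non-attenders. Maintenance sessions are offered at 12, 24 and 36 months, and the article does not bar initial non-attenders from them. Attendance alone also does not capture text uptake, which is what distinguishes Walking Away Plus. A text-based definition of receipt would be worse, since people who decline or stop texts may still have had the education, a pedometer and calls.

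The differing filters do follow from differing interventions, and the article does not say that the active arms will be compared per-protocol. But the rule is fully stated rather than left open, so an analysis plan that is not shown could add to it or relabel it, but would not make the rule as written sound.

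**Conclusion.** The point holds as a limited one. The stated rule filters the active arms on adherence, more strictly in Walking Away Plus, and leaves controls unfiltered. Its result is open to selection bias whenever adherers and non-adherers differ in prognosis. The bias is 0 to 400 steps/day for 10–40% removed and a gap of 0–1000 steps/day. Both ranges are assumptions, and an upward direction is probable rather than shown. The formula further assumes that assignment does not affect those removed, which is doubtful for participants removed only for stopping texts. The primary comparison stays valid in this respect, and the sample size reproduces exactly and does not change.

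**What to change.** For each active arm against control, add a CACE estimate as the main adherence analysis: two-stage least squares with randomised arm as instrument, attendance at the initial Walking Away session as receipt, and baseline covariates. The covariates need listing, because the two that Data analysis names (accelerometer wear time and number of valid days) are not baseline characteristics.

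If the per-protocol analysis is kept:
- label it exploratory and not protected by randomisation;
- do not present it as a robustness check on the primary result;
- do not use it to compare the two active arms.

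Report text registration, STOP messages and session attendance over the four years descriptively.

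The cost is wording and one further model, since the adherence data are already planned. The downsides are a wider interval (SE about 405 against 344 at 80% attendance) and an exclusion restriction that weakens if initial non-attenders come to later maintenance sessions. A CACE on complete cases also leaves missing outcomes unaddressed.

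### As worded, the plan carries accelerometer wear covariates into the models for blood and body measurements, and so leaves out people who have a clinic result but no valid recording

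*Protocol article*

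**What the plan says.** The Data analysis section of the protocol article compares change in physical activity between groups by multiple linear regression, "after adjusting for potential areas of bias between groups, valid accelerometer wear time and the number of valid wear days". On the analysis set it says: "The primary analysis will be based on analysing those with complete data at each time point in the group to which they were randomised". Missing data are otherwise handled only in a secondary role: "A sensitivity analysis will be undertaken to assess the impact of imputing missing data through multiple imputation".

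The next paragraph of that section deals with the clinic outcomes in one clause: "secondary biochemical and anthropometric outcomes will be analysed using the same strategy and at the same time-points as that described for the primary outcome". It does not set aside any part of the primary model.

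The Primary outcome section under Study outcomes explains the wear covariates. The reason given is "Due to the potential for bias between groups in factors used to acquire valid accelerometer data", and the consequence is that "average wear time and the number of valid days will be included as covariates in the analysis". The validity rule is there too: "At least three days valid wear is required to count as a valid recording".

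**The concern.** Wear time and valid days correct a step count for how long the device was on the body. They have no such role for a venous sample, a weight or a tape measurement. If they enter those models, two things follow.

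- **Conditioning on post-randomisation behaviour.** Wear at follow-up happens after allocation. The interventions promote activity and self-monitoring, so wear could plausibly differ by arm. Adjusting a metabolic outcome for it can absorb part of the treatment effect or distort the comparison.
- **Loss of valid results.** In a complete-case regression a missing covariate removes the person. Someone who attended clinic and gave blood, but did not return a usable recording, would not contribute to the HbA1c estimate. Those who remain would be selected on compliance with the device.

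At stake are the randomised comparisons for the glycaemic, lipid and anthropometric outcomes.

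**Working it through.** This is mainly a matter of setting the passages together. Arithmetic is needed only to see whether a size can be given.

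**1. What the clinic outcomes inherit.** The primary strategy in Data analysis consists of two comparisons with control, regression of change, adjustment, complete cases as randomised, interactions and ethnic strata, and imputation and per-protocol sensitivity analyses. The adjustment has three parts: an unspecified group of potential biases, wear time, and valid days. The last two are the only covariates named specifically. The clause on clinic outcomes takes over the strategy whole.

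**2. Whether a participant can have a clinic result without a recording.** Yes. Blood and body measurements are taken at the visit. The accelerometer is worn for the seven days after the visit, posted back, and counts only with at least three valid days. The two kinds of data can therefore be missing separately.

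**3. Whether the main estimate is protected.** No. The main analysis is complete-case. Multiple imputation could retain such participants, but only in the sensitivity analysis.

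**4. Whether the stated reason for the covariates reaches the clinic outcomes.** No. The Primary outcome section ties them to obtaining valid accelerometer data. This means the literal model has no stated purpose for a blood test. It also gives the best ground for reading the clause more narrowly.

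**5. Whether the loss can be sized.** The plan's own figure comes first. The inputs from the Sample size section are a 1000 steps/day difference, SD 4000, power 0.8, "alpha = 0.025 (allowing for 2 a priori comparisons against control conditions"), and 30% drop-out. Sidedness is not stated; two-sided reproduces the figure.

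- Evaluable per group: n = 2 × (2.241 + 0.842)² × (4000/1000)² = 2 × 9.505 × 16 ≈ 304.2, rounded up to 305.
- Randomised per group: 305 / 0.7 = 435.7, rounded up to 436. Total: 3 × 436 = 1308. Both match the article.

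So 305 is the number evaluable for the step-count outcome. It is not stated to be the number of clinic attenders with a blood or weight result. Nor is it the base for fasting and 2-hour glucose, which Table 4 limits to Leicester. The article gives no rate of invalid or missing recordings among attenders, so the number with a clinic result but no recording cannot be derived.

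**6. Whether an 80% power baseline applies to these outcomes.** For lipids, weight and waist no power target is stated. For HbA1c the article claims 80% power for a 0.25% difference even within ethnic groups. Take that claim at face value, with a South Asian stratum of 25% of 305, about 76 per arm:

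- Implied standardised difference: 3.083 × √(2/76) = 0.500.
- Whole cohort at 305 per arm: 0.500 × √(305/2) − 2.241 = 6.18 − 2.24 = 3.94, which is power above 99%.
- At 259 per arm (305 less 15%): 0.500 × √(259/2) − 2.241 = 5.69 − 2.24 = 3.45, still above 99%.

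On the plan's own claims, 80% is not the starting point for HbA1c in the whole cohort.

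**The case against.** The strongest reply is that the article nowhere puts wear time into an HbA1c or weight model and nowhere requires a recording for those outcomes. Strategy can mean the comparisons, the regression of change, the analysis set and the sensitivity analyses, with covariates suited to each outcome. The Primary outcome section gives an accelerometer-specific reason for the covariates, and a careful statistician would probably leave them out of a blood-test model. This is also a condensed article, and an analysis plan that is not shown may list covariates by outcome.

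Much of this stands. It makes the loss of participants conditional on the literal reading. It does not remove the point, because the article does not leave the matter open: it states a rule, and the rule followed literally gives the wrong model. An analysis plan written from that sentence could inherit the fault.

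Two stronger inferences are tempting and are not supported:

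- **A power loss.** A reader might take an assumed 10–15% off 305 per arm, reach about 275–259, and conclude that power falls from 80% to about 75–73%. The rate has no source in the documents. The 305 may already exclude people without a valid recording, so the loss could be counted twice. The 80% baseline also fails for HbA1c, as the last step of the working shows.
- **An expected difference in wear between arms.** The article speaks only of a potential for bias between groups and does not predict a difference.

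**Conclusion.** The point holds as a fault of wording with a real consequence on one of its two readings. As written, the clause makes clinic outcomes depend on device wear and drops people with valid results from the main analysis. On the narrower reading neither happens.

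The size of any loss or bias cannot be derived from the documents, and the direction of any bias is also unknown. The conclusion rests on three things: the absence of any exception in Data analysis, the complete-case main analysis, and the fact that clinic and accelerometer data can be missing independently. It assumes nothing about how many participants are affected. The ambiguity is worth closing before results are known, since it would otherwise leave a choice between two models and two analysis sets for every biochemical and anthropometric outcome.

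**What to change.** State in the analysis plan that average wear time and number of valid days are covariates for accelerometer-derived outcomes only. State also that each biochemical and anthropometric outcome is analysed, as randomised, in all participants with that outcome measured, whether or not they have a valid recording. Adjust each model for the outcome's own baseline value and for the randomisation strata, which the Randomisation section gives as sex and ethnicity. The baseline and strata adjustment improves on the stated model at no cost; removing the wear covariates is the correction itself.

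The change is a sentence or two of wording. It needs no new data and no budget, and it does not touch the primary analysis.
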